# A multi-center, single-blinded, randomized, parallel-group, superiority study to compare the efficacy of manipulation under anesthesia versus intra-articular steroid injection in the treatment of patients with frozen shoulder and a diagnosis of rotator cuff injury or tear by MRI: study protocol for a randomized controlled trial

**DOI:** 10.1186/s13063-023-07810-2

**Published:** 2023-11-27

**Keywords:** Adhesive capsulitis, Frozen shoulder, Rotator cuff injuries, Manipulation under anesthesia, Intra-articular steroid injection

## Abstract

**Background:**

Frozen shoulder (FS) is a common condition that can cause severe pain and limited range of motion in the shoulder joint. While intra-articular steroid injection has been shown to be an effective treatment for FS, manipulation under anesthesia (MUA) is an alternative treatment that has gained popularity in recent years. However, there is a lack of evidence regarding the effectiveness of MUA on FS patients with concomitant rotator cuff injury or tear. Though a few studies have shown that MUA is not associated with rotator cuff tears, and will not exacerbate the injury, more high-quality studies with bigger sample sizes are needed. Therefore, the aim of this multi-center, single-blinded, randomized, parallel-group, superiority study is to compare the efficacy of MUA versus intra-articular steroid injection in the treatment of FS patients with a diagnosis of rotator cuff injury or tear by MRI.

**Methods:**

A parallel, single-blinded, multi-center randomized controlled trial of 320 patients will be conducted at three hospitals of China. Eligible patients with frozen shoulder and rotator cuff injury or tear diagnosed by MRI will be randomly assigned to, in equal proportions, the manipulation under anesthesia group and the intra-articular steroid injection group via a central randomization system, undergoing a corresponding operation on day one and a sequent physical exercise for 14 days. The primary outcome is the comprehensive efficacy evaluation (total effective rate) and the change of Constant-Murley Score. Outcome assessors and data analysts will be blinded, and participants will be asked not to reveal their allocation to assessors.

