##### Post-procedural physiotherapy (PPP)

Patients from both groups will initiate a 14-day functional exercise, starting on the first day after the intervention treatment. A uniformly and strictly trained physician guides the first functional exercise of the patients until the patients and their accompanying family members have mastered the correct exercise method. They can record relevant videos, and family members can assist and supervise patients in the initial exercise stage. Physicians follow up with patients regularly to ensure the standardization and correctness of exercise posture.

The specific methods are as follows:①Forward elevation: The patient stands facing a wall with their feet shoulder-width apart and toes touching the wall. The fingers of the affected arm are spread out and placed on the wall. Slowly elevate the arm along the wall until the limit of pain tolerance is reached. The unaffected arm can assist in lifting the affected arm, or another person can push the scapula of the affected side from behind to help raise the arm to the maximum position.②Forward flexion with shoulder support: The affected shoulder is flexed to 90° with the elbow flexed. The palm of the unaffected hand is gradually placed on the elbow, moving it towards the midline to bring the affected arm to rest on the opposite shoulder joint.③Extension with internal rotation: The patient sits or stands with the palm of the affected hand facing backward and extends the shoulder joint. Within the limit of pain tolerance, gradually rotate and adduct the affected arm while bending the elbow until the fingers touch the opposite scapula. The unaffected hand can assist the affected hand in completing the exercise.

Repeat the above movements after the patient’s pain is relieved. Perform three sets of each exercise, three times per day.

The ROM, CMS, MPQ, VAS, and PPI numbers or scores will be collected at 1 day, 2 weeks, 4 weeks, 12 weeks, and 24 weeks after the intervention. Additionally, imaging examinations will be conducted during the 24-week visit. Due to the nature of the physical examinations required, all follow-up time points must be completed by the patients at the hospital’s outpatient or inpatient departments.

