### Outcomes {12}

#### Primary outcome measures

##### Comprehensive efficacy evaluation (total effective rate)

Assessment was made primarily with reference to measurements of external range of motion of the glenohumeral joint and improvement in pain.

The specific judgment is as follows:①Cured: Shoulder pain disappears, forward flexion>150°, abduction>120°, extension>45°, and internal and external rotation>60°.②Effective: Shoulder joint pain basically disappears, with forward flexion from 120° to 150°, extension from 30° to 45°, abduction from 90° to 120°, and external and internal rotation from 45° to 60°.③Improved: Shoulder pain is reduced, and the range of motion is increased compared with that before treatment, but there is still limitation of movement.④Ineffective: no change in indications and symptoms before and after treatment.

The total effectiveness rate = (cure + effective + improved) / number of patients × 100%

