#### Constant–Murley Score (CMS)

The CMS provides an assessment of both Individual parameters and clinical symptoms, which is sufficiently sensitive to reveal even small changes in function [51]. The score consists of four domains [52]: pain (15 points), activities of daily living (20 points), movement (40points), and strength (25points). The patients self-assess the pain and the first three questions of activities of daily living, and all other items are examiner assessed.

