### Sample size {14}

The total effective rate is the primary outcome parameter. This is based on the efficacy of previous studies on MUA [56] and intra-articular steroid injection [57] in the treatment of FS. The sampling ratio for the treatment and control groups is 1:1, and the number of test subjects required for each group sets as *n*, using a two-sided test. πT and πC are the reference values for the efficacy of previous studies on MUA and steroid substance shoulder cavity injection for FS, respectively [56, 57], setting πT = 0.862 and πC = 0.428. Based on these parameters, we calculated a sample size of 160 subjects per group with a power of 80%, alpha 0.05, and a 10% drop out rate.

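### Two primary outcomes in the abstract and outcomes section, one in the sample-size section, and no visit for the CMS change: control of the 5% error rate is not established

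*Protocol article*

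**What the plan says.** **Two primaries.** The abstract's Methods paragraph reads: "The primary outcome is the comprehensive efficacy evaluation (total effective rate) and the change of Constant-Murley Score". In Outcomes {12}, the plural heading "Primary outcome measures" is followed by the total effective rate and then by CMS, and only after that by the heading for secondary outcomes. The CMS entry opens "The CMS provides an assessment of both Individual parameters and clinical symptoms" and goes on to its domains and who scores them. It gives no visit and does not define the change.

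**One primary.** Sample size {14} says "The total effective rate is the primary outcome parameter". It specifies "using a two-sided test", takes the planning rates by "setting πT = 0.862 and πC = 0.428", and reports that "we calculated a sample size of 160 subjects per group with a power of 80%, alpha 0.05, and a 10% drop out rate". CMS plays no part in it. The Discussion also refers to the primary outcome measure in the singular.

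**Visits.** The physiotherapy section gives the follow-up schedule: "The ROM, CMS, MPQ, VAS, and PPI numbers or scores will be collected at 1 day, 2 weeks, 4 weeks, 12 weeks, and 24 weeks". Table 1 marks CMS on the treatment day and at all five follow-up visits, but marks the total effective rate only at 24 weeks.

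**Analysis.** Statistical methods, Outcomes {20a}, plans repeated-measures ANOVA for follow-up data, with a rank sum test as the fallback, and logistic regression relating treatment to efficacy. It singles out no primary CMS contrast.

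**The concern.** Which outcome is primary, and when it is measured, are protocol-level choices. Here the article states the first in two incompatible ways and leaves the second open for CMS. The 0.05 is attached to one outcome, while two are called primary.

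What is at stake is the meaning of a positive result. If the total effective rate shows no difference but CMS does at some visit, a reader relying on the abstract could call the trial positive and a reader relying on the sample-size section could not. Trial status gives a recruitment start of 1 January 2023, so the longer the choice stays open, the more data will exist when it is made.

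**Working it through.** **1. The plan's own figure.** Inputs from Sample size {14}: rates 0.862 and 0.428, two-sided alpha 0.05, power 80%, 1:1 allocation, 10% dropout. The mean rate is (0.862 + 0.428)/2 = 0.645.

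n per group = [1.960 × √(2 × 0.645 × 0.355) + 0.842 × √(0.862 × 0.138 + 0.428 × 0.572)]² / (0.862 − 0.428)² = [1.960 × 0.6767 + 0.842 × 0.6031]² / 0.434² = 17.9, so 18 evaluable, and 18/0.9 = 20 with dropout.

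The stated 160 is not reproduced. With a continuity correction the result is 23 evaluable, or 26 with dropout. That gap is a separate matter. It counts here only because it shows how much room there is for a smaller alpha on the total effective rate. Evaluable patients at the stated size: 160 × 0.9 = 144 per group.

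**2. Error rate under each reading the article leaves open** (no true difference on either outcome, each test two-sided at 0.05)

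| What counts as success | False-positive rate |
|---|---|
| Total effective rate alone is primary | 5% |
| Both outcomes must succeed | at most 5% |
| Either of the two, independent tests | 1 − 0.95² = 9.75% |
| Either of the two, correlation 0.5 (bivariate normal) | 9.1% |
| Either of the two, correlation 0.8 | 7.8% |

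The both-required bound follows because the chance that both tests reject cannot exceed the chance that either named one does. It also holds when only one of the two outcomes truly differs.

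**3. Upper scenario.** This is the total effective rate plus a separate CMS test at each of five visits, any one sufficient, six tests in all.

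| Common correlation (assumed) | False-positive rate |
|---|---|
| 0 | 1 − 0.95⁶ = 26.5% |
| 0.5 | 20.7% |
| 0.7 | 16.4% |
| 0.8 | 13.9% |

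The documents give no correlations, so every non-zero value in both tables is an assumption.

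**4. Cost of splitting alpha.** At 0.025 the critical value is 2.241, and the formula in step 1 gives n = 21.8, so 22 evaluable, and 22/0.9 = 24.4, so 25 with dropout. At 144 per group, the power for the total effective rate on the plan's own rates is Φ[(0.434 × √144 − 2.241 × 0.6767)/0.6031] = Φ(6.12), above 99.9%. Power for CMS cannot be computed, because the article gives neither a difference nor a standard deviation.

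**The case against.** A reader might infer from two primaries and a single alpha that the 5% error rate is broken. The documents do not support that. The 0.05 is stated only for the total effective rate, and for that outcome it is held. The abstract joins the two outcomes with the word and, which can be read as requiring both, and then the rate also stays at or below 5%. No section says that either outcome alone is enough. This part of the objection stands.

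A reader might also take the six-test figures as the trial's actual error rate. They rest on five separate CMS tests, any one sufficient, and on assumed correlations. Outcomes {20a} plans a repeated-measures ANOVA, which could give a single overall CMS test. Its wording does not settle the matter, so those figures are an upper scenario only.

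It can further be said that this is a journal article, that success rules and alpha splits commonly sit in an analysis plan, and that sizing a trial on one of two primaries is not an error. That is fair for the missing rule and for the sizing. It does not remove the conflict over how many primaries there are, because the article makes both statements itself. The Discussion's singular is loose prose and carries little weight.

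Finally, the choice of CMS visit belongs to the sponsor. Objectives {7} hypothesises quicker functional recovery, so week 24 is not the obvious visit.

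**Conclusion.** The inconsistency is real and sits at protocol level: two primaries in the abstract and Outcomes {12}, one in Sample size {14}, and no visit among five for the CMS change. The supported conclusion is that control at 5% is not established, not that it is lost. The rate is at most 5% under two admissible readings and up to 9.8% if either outcome suffices. The 9.8% assumes independent tests, and positive correlation lowers it. It is higher again only under the upper scenario of five separate CMS claims. The article excludes none of these readings. This should be corrected, but it does not by itself invalidate the design.

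**What to change.** Make the abstract, Outcomes {12}, Sample size {14} and the Discussion state the same rule, and name one CMS visit or one overall CMS contrast. Any of these would hold 5%:

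- **Fixed sequence.** Test the total effective rate at week 24 first at two-sided 0.05, which agrees with Sample size {14} and Table 1. Test CMS change at one pre-named visit at 0.05 only if the first test is significant. The downside is that CMS cannot be claimed if the first test fails.
- **Both required.** Each is tested at 0.05 and success needs both. The trial's power is then limited by CMS, for which the article gives no planning values.
- **Split alpha.** Each is tested at 0.025. Either can then be claimed alone, and on the plan's own rates the total effective rate loses almost no power at 144 per group.

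None of these needs more patients for the total effective rate. The text change is short. If it counts as a change to objectives or design, Protocol amendments {25} requires a formal amendment, agreed by the Science and Technology Commission and approved by the ethics committee, while recruitment is under way. The choice of rule and visit should be made without sight of outcome data by treatment group.

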**Discussion:**

This study aims to explore the superiority of manipulation under anesthesia in reducing pain and improving shoulder function in frozen shoulder patients accompanied with rotator cuff injury. To provide a scientific basis for the dissemination and application of manipulation under anesthesia, and a better knowledge for the role of MUA in the treatment of frozen shoulder accompanied with rotator cuff injury.

**Trial registration:**

Chictr.org.cn ChiCTR2200067122. Registered on 27 December 2022. ChiCTR is a primary registry of the World Health Organization International Clinical Trials Registry Platform (WHO ICTRP) network and includes all items from the WHO Trial Registration data set in Trial registration.

## Background and rationale{6a}

Frozen shoulder (FS), also known as “adhesive capsulitis” [1], “fibrotic capsulitis” [2], “primary idiopathic stiff shoulder” [3], and “contracture of the shoulder” [4], is a common shoulder concern manifesting in progressive loss of glenohumeral movements coupled with the painful, debilitating contraction of the shoulder [5, 6]. It is a retrogressive progress of the fibroproliferative tissue, and in spite of the dissections owing to the immunobiological advances in other diseases of this condition, the molecular pathophysiology underpinning the idiopathic FS is still poorly understood [7–10]. Idiopathic FS is characterized by a spontaneous onset of pain and stiffness of the shoulder, especially a loss of external rotation, without a prior traumatic event [11]. In May 2014, the International Society of Arthroscopy, Knee Surgery and Orthopedic Sports Medicine (ISAKOS) first proposed and published an expert consensus on frozen shoulder at the meeting held in Amsterdam which defined “frozen shoulder” as a limited range of motion of the glenohumeral joint due to various primary or secondary causes, clinically characterized as pain around the shoulder, with a reduced active and passive range of motion [12].

FS is a common cause of shoulder pain and disability. It affects approximately 2–4% of the general population [13]. Epidemiological surveys show that the prevalence increased linearly with age whilst incidence peaked at around 50 years old [14], more women than men, with an incidence of 3–5% in the general population [15], accounting for 42% in shoulder diseases, approximately 8% in orthopedic diseases [16]. Despite that many study show it is a self-limiting disease, a reversible condition, with a course of 1–3 years [17–19], this is an estimated time frame, many patients can still experience symptoms at 6 years [20]. If the shoulder’s adhesion is severe and is not treated in time, 6–17% of the patients will affect the healthy side within 5 years [21], which will seriously influence patients’ daily work and quality of life, and even lead to a loss of motor function of the shoulder. MUA (manipulation under anesthesia) is one of the most common surgical approaches for treating frozen shoulder [22]. It involves the passive tearing of the thickened inflamed capsule and contracted ligaments [23]. Originally performed under general anesthesia, now with the recent advancements in ultrasound technology are performed under brachial plexus or cervical nerve root blocks as well [24, 25]. It is the most cost-effective option [26, 27], with satisfactory short- and long-term results in ROM (range of motion), pain, and function [28–30].

Rotator cuff injury or tear is a common chronic pathology that can be initially asymptomatic and may remain unknown for a long period of time, varying from person to person. The prevalence of asymptomatic rotator cuff tears ranges from 8 to 46% [31, 32], and the prevalence of rotator tears concomitant with frozen shoulder ranges from 12.3 to 41.7% among all RC tears [33]. For frozen shoulder patient’s concomitant with RC injury intending to undergo an MUA operation, the fear of further iatrogenic rotator cuff tears exists. Although a few studies have shown that MUA is not associated with rotator cuff tears [34], and will not exacerbate the injury [35], clinically, many physicians still have concerns and exclude the patients for MUA if they have rotator cuff injury or tear on MRI [36].

Currently, there are many methods to treat FS in both conservative and surgical ways. The goal is to relieve pain and limited mobility, shorten the course of the disease, improve the patient's personal life quality, and increase social participation. Treatments for FS include conservative treatments such as NSAIDs, physical rehabilitation therapy, and intra-articular steroid injection, or invasive treatments such as manipulation under anesthesia (MUA), arthroscopic capsular release, and hydro-dilatation [36]. However, systematic reviews indicate that there is insufficient evidence and no agreement on which procedure is superior [37, 38]. What is more, when it comes to FS patients combined with rotator cuff injury, there is a shortage of high-quality comparative studies on these procedures.

The popularity of resonance examination has made the diagnosis of rotator cuff injury (or tear) more common. It is found the overall prevalence of tears in asymptomatic individuals is 34% by MRI [23] and 23% of full-thickness rotator cuff tears by ultrasound, with 51% of individuals over age 80 having tears [39]. This imagined diagnosis does not necessarily connect to the sudden onset of the stiffness and pain of the shoulders. In clinical practice, some doctors and patients become overly fixated on the results of magnetic resonance imaging (MRI), abandoning more simple and inexpensive treatment options like MUA, leading to overreliance on arthroscopic surgery for treatment [40]. However, while this approach can reduce pain to some extent [41], the surgery itself may worsen the stiffness of frozen shoulder due to surgical trauma [42, 43].

The Orthopedic Department of Shanghai Shuguang hospital has applied MUA since 2011. At present, more than 1000 cases of FS have been successfully treated by MUA, and the treatment has been carried out in Shanghai First People’s Hospital, Shanghai Baoshan District Central Hospital with same remarkable results.

During treatment, we have discovered that many patients with classic frozen shoulder symptoms also have, diagnosed by MRI scans, a rotator cuff injury or tear. Interestingly, these patients did not experience any symptoms related to their rotator cuff prior to their frozen shoulders’ sudden onsets, and after undergoing manipulation under anesthesia (MUA) treatment, their rotator cuff injury did not worsen. The current studies exploring FS combined with rotator cuff tears or injuries offered limited information on the treatment options available and on their relative effectiveness compared to each other [34, 44, 45]. A deeper comprehension of the available treatment methods, technical considerations, and risks would help clinicians create appropriate treatment plans for this situation. Due to the apparent lack of knowledge in this area, the objectives of this study are to address this gap by examining more available treatment modalities and their outcomes.

### Explanation for the choice of comparators {6b}

Intra-articular steroid injection is a common treatment of FS [37], providing short-term benefits [37, 46, 47], and also proving effective for rotator cuff tear [48]. It is an effective, common, affordable treatment with little direct transformation to the shoulder structure, that is why we choose it as our control group’s treatment.

## Objectives {7}

The objective of this trial is to observe the safety and efficacy of MUA, compared to intra-articular steroid injection, in the treatment of FS patients diagnosed with rotator cuff injury or tear by MRI. We hypothesize that the course of the disease can be shortened by MUA with quicker functional recovery and gain in the range of motion and a subsequent faster return to work compared to steroid injection treatment. Also, preoperative and sequent MRI and musculoskeletal ultrasounds will be applied to patients before and 6 months post the intervention to evaluate the condition of the patient’s rotator cuff injury or tear.

## Trial design {8}

This trial is a randomized, controlled, prospective, multicenter superiority trial with two parallel groups. Patients with FS accompanying MRI diagnoses as rotator cuff injury or tear are randomly divided into two groups: the trial group (with manipulation under brachial plexus block anesthesia as the main intervention) and the control group (with intra-articular steroid injection as the main intervention). All patients included in this study will undergo a program of shoulder exercises, normally commencing within 24 h after the corresponding intervention, with three sessions per day lasting for 2 weeks. The data will be collected before the intervention, 1 day, 2 weeks, 4 weeks, 12 weeks, and 24 weeks after the intervention. Randomization will be performed by a computer-generated random number table with a 1:1 allocation.

## Methods

### Study setting {9}

This trial is organized and implemented by the Department of Orthopedics and Traumatology of Shuguang Hospital in Shanghai, China, affiliated with Shanghai University of Traditional Chinese Medicine. The research is planned to be completed in three hospitals: (1) Shuguang Hospital Affiliated with Shanghai University of Traditional Chinese Medicine, (2) Shanghai First People's Hospital, and (3) Shanghai Baoshan District Hospital of Integrated Traditional Chinese and Western Medicine. All three hospitals are grade III, class A comprehensive hospitals in Shanghai, China. Shanghai First People’s Hospital is in the city center area, while Shanghai Baoshan District Hospital of Integrated Traditional Chinese and Western Medicine is located in rural areas, and Shuguang Hospital is located between urban and rural areas. All three hospitals in Shanghai are renowned for their departments of orthopedics and traumatology, and Shi's Orthopedics and Traumatology Department of Shuguang Hospital collaborates frequently with the other two hospitals on scientific research projects. By utilizing a practical trial design and involving a broad range of clinicians, the study’s results will be both applicable and generalizable.

